**Fig. 1 Fig1:**
[figure not shown]
Flowchart of randomized clinical trial. IG1, intervention group 1; IG2, intervention group 2; PFM, pelvic floor muscles; PFMT, pelvic floor muscle training; NMES, neuromuscular electrical stimulation

Two physiotherapists specialist in Women's Health will carry out, guide, and apply the interventions. They will not be involved in the participants’ randomizations, evaluations, or reevaluations. The flowchart is presented in Fig. 1, and the schedule of registrations, interventions, and evaluations are presented in Fig. 2.

**Fig. 2 Fig2:**
[figure not shown]
Schedule of registrations, interventions, and evaluations. IG1, intervention group 1; IG2, intervention group 2; PFMT, pelvic floor muscle training; NMES, neuromuscular electrical stimulation; -*t*_1_, subscription of participants; *t*_0_, allocation and initial assessment of participants; *t*_1_, intervention; *t*_2_, re-assessment after finished the intervention protocol; *t*_3_-*t*_8_, follow-up. Asterisks symbol indicates the following: recommended content and elaboration by SPIRIT 2013 for protocols [15]

### Interventions

Ten treatment sessions will be held, once a week, with a total of 10 weeks of attendance. The participants will be instructed to perform the protocol daily at home. The CG (control group) will receive an orientation booklet for the proposed protocol. The IG1 will perform PFM protocol with physiotherapist supervision 1 time a week and will be instructed to perform the exercise at home without supervision, and the IG2 will perform the PFM protocol (only in supine/lying position) associated with the intravaginal NMES technique with a physiotherapist supervision for 20 min, once a week.

PFM will be performed as the protocol proposed by Bø, Talseth e Holme [33]:
Positions: lying, kneeling, sitting, and standing;Series: 1 series of exercise for each position;Repetitions: 12 sustained contractions with 6 s of duration;Rest: 6 s;After repetitions of sustained contractions, 4 fast contractions are added;Intensity: maximal voluntary contraction;Session duration: 45 min.

The intravaginal NMES technique, applied to IG2, will be performed with the Dualpex 961 equipment (Quark Medical Products), following the description of the parameters suggested by the study conducted by Barbosa et al. [34]. The participants will remain in supine position, with flexion of the hips and knees. The physiotherapist responsible for the interventions will wear procedure gloves during the entire session and will apply lubricating gel on of the vaginal probe that will be introduced into the participant’s vaginal canal. During the period of NMES application, the physiotherapist will fix the probe manually. At the end of study, vaginal probes will be discarded. The parameters used during NMES application are described in Table 3. In the first 5 treatment sessions, the ON time stimulus will be fixed in 5 s, and the OFF time stimulus will be 15 s. For the last five treatment sessions, the OFF time stimulus will be decreased to 10 s.

**Table 3 Tab3:** Randomized controlled blinded ES parameters

	1–5th session	6–10th session
Phase duration (μs)	700	700
Frequency (Hz)	50	50
Ramp-up (s)	1	1
Stimulus on time (s)	5	5
Ramp-down (s)	0	0
Stimulus off time (s)	15	10
Duty-cycle ratio	1:3	1:2
Time (min)	20	20

μs, microseconds; Hz, Hertz; s, seconds

During the first five treatment sessions, IG2 will perform 4 series of 12 sustained voluntary contractions of 6 s with 4 fast contractions added to the end of the protocol and 50 s of rest at the end of each series, according the 1:3 duty-cycle ratio. At the last five treatment sessions, participants will perform the same protocol; however, the duty-cycle ratio will decreased to 1:2, and subjects will perform 4 series of 12 sustained contractions for 6 s with 4 fast contractions, with 1 min and 50 s of rest at the end of each series.

To perform the contractions protocol, at the beginning of the “on time” (indicating the current flow), the physiotherapists responsible for the interventions will give the following verbal instruction to the participant: “contract, 1, 2, 3, 4, 5, 6, relax.” At the end of each series of sustained contraction, the participants will be instructed to perform fast contractions with the following command “contract-relax, contract-relax, contract-relax, contract-relax.” Four series will be completed as equivalent to the 4 positions proposed by Bø, Talseth e Holme [33] during the PFMT protocol (standing, sitting, kneeling, and lying). During each rest period, participants will be asked if the intensity of NMES can be increased and in all sessions the values of the intensities at the beginning and at the end of the sessions will be recorded. Figure 3 presents the sequence of intervention sessions.

**Fig. 3 Fig3:**
[figure not shown]
Scheme of the numbers of sustained, fast contractions, and rest time of the sessions of intravaginal electrical stimulation

The presence of any adverse effects or pain and discomfort related to the application of the NMES will be considered as the criterion to discontinue the treatment. Participants will be instructed to immediately communicate the researcher responsible for the data collection in any case of adverse effect.

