### Blinding

In view of the impossibility of blinding the participants in relation to the interventions, the blinding will happen among the physiotherapists, taking into account the evaluation and intervention. The physiotherapist who will carry out the evaluation will not have the information of the participants’ allocation, and the physiotherapists responsible for guide the interventions will not have the information referring to the evaluations and reevaluations of the participants.

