### Data management

The data will be collected on paper and stored in folders in an office allocated at the Women’s Health Research Laboratory (LAMU), in Federal University of São Carlos. The data will be entered into the Excel software by the physiotherapist responsible for evaluations, reevaluations, and follow-up. In addition, all the data will be available in a public research bench.

The database and electronic analyzes will be stored on a secure computer server, with personal login access authorized by the principal investigator of the present study. The principal investigator will have access to the complete data set (without the allocation groups), and the co-investigators will have access to data when necessary. Upon completion of the study, all study data and documents will be archived by the main researcher of this study for 5 years at the Physiotherapy Department at Federal University of São Carlos.

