At the interview and physical assessment, the subjective interview record will be applied, which generates qualitative variables that will be presented as frequencies and percentages and quantitative variables that will be presented as minimum value, maximum value, mean, median, and standard deviation. One researcher will perform the vaginal palpation and the manometry assessment, as well as applied SF6-D, KHQ, King´s Health Questionnaire for Scoring Algorithm, health cost analysis form, and 24 h-voiding diary, which will result in quantitative scales that will be presented as minimum value, maximum value, mean, median, and standard deviation.At the end of treatment sessions, vaginal palpation and manometry will be repeated, as well as SF6-D, KHQ, King’s Health Questionnaire for Scoring Algorithm, health cost analysis form, and the 24 h-voiding diary, which will result in quantitative scales that will be presented as minimum value, maximum value, mean, median, and standard deviation.At the 1st to the 6th month of follow-up, the health cost analysis form will be applied, and at the 3rd and 6th month of follow-up, the SF6-D, KHQ, King´s Health Questionnaire for Scoring Algorithm, and health cost analysis form will be completed, which will result in quantitative scales that will be presented as minimum value, maximum value, mean, median, and standard deviation.At the end of the treatment, the ANOVA for repeated measurements will be applied to verify the effects of the three groups and the two stages (pre-treatment and re-assessment after finished the intervention protocol) and the interactions between them according the results related to the vaginal palpation, manometry, SF6-D, KHQ, King´s Health Questionnaire for Scoring Algorithm, health cost analysis form, and 24 h-voiding diary, if the residues present normality. If the residues do not present normality, a non-parametric test will be applied.At the end of the follow-up, the repeated measures ANOVA will be applied to verify the effects of the three groups and the eight stages (pre-treatment, re-assessment after finished the intervention protocol and 1, 2, 3, 4, 5, and 6 months of the follow-up) and the interactions between them considering the SF6-D, KHQ, King’s Health Questionnaire for Scoring Algorithm, health cost analysis form, and 24 h-VD, if the residues present normality. If the residues do not present normality, a non-parametric test will be applied.The cost-utility assessment will be performed by the quality-adjusted life years (QALY), which combines the length and quality of life into a single index number between 0 and 1, where 0 corresponds to a health state judged to be equivalent to death and 1 corresponds to optimal health [35, 36]. To conduct the statistical analysis, the mean between-group cost differences will be corrected for their baseline, and the total costs will be divided by the costs differences for incremental analysis of cost-effectiveness and cost-utility ratios. Subsequently, a deterministic cost-utility value and a probabilistic one will be determined by applying a bootstrapping technique of 5000 interactions and the bias-corrected, in order to compare health costs between groups. The results will be presented with the confidence interval of 95% (95% CI). The likelihood of the cost-effective intervention will be estimated by the cost-effectiveness acceptability curves to compared values other than willingness to pay [37]. The Kaplan-Meier method and the Log-Rank between-group comparison test will be applied in order to assess the sensitivity of the uncertainty of each parameter by assessing the changes in the results in the range of parameter values [38].

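### Adverse effect reports go to the researcher who collects the data, apparently the blinded assessor, so an NMES complaint can reveal allocation before the post-treatment assessment

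*Protocol article*

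**What the plan says.** At the end of the Interventions section, any adverse effects, or "pain and discomfort related to the application of the NMES will be considered as the criterion to discontinue the treatment". The next sentence gives the reporting line: "Participants will be instructed to immediately communicate the researcher responsible for the data collection in any case of adverse effect". No other contact for adverse effects is named.

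The Blinding section says: "The physiotherapist who will carry out the evaluation will not have the information of the participants’ allocation". The same section concedes that the women cannot be blinded.

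Other sections describe who does what:

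- **Statistical analysis plan:** "One researcher will perform the vaginal palpation and the manometry assessment". The same person applies the SF-6D, the KHQ, its scoring-algorithm version, the cost form and the voiding diary.
- **Data management:** "The data will be entered into the Excel software by the physiotherapist responsible for evaluations, reevaluations, and follow-up".
- **Randomization and allocation**, on the two treating physiotherapists: "They will not be involved in the participants’ randomizations, evaluations, or reevaluations".
- **Auditing:** the laboratory coordinator takes no part in any data collection step.
- **Harms auditing:** the medical records of all participants are reviewed, and treatment-related harms are reported and classified by severity.

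**The concern.** The Trial design section presents this as a trial with a blind assessor. The reporting line in Interventions appears to lead to that assessor, and the complaints most likely to travel along it concern a treatment that only one arm receives. Any loss of blinding would thus fall on IG2 and not evenly across arms. It would arise during the 10 weeks of treatment, before the assessor grades palpation, coaches the manometry contractions and applies the questionnaires at the end of treatment.

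What is at stake is assessor-side bias in the comparison of IG2 with the other two arms, on the measures that depend on the assessor.

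**Working it through.** The article states no figure on this point, so the check sets its sections side by side.

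**1. Who is the researcher responsible for data collection?**

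| Role | Described in | Fits? |
|---|---|---|
| Treating physiotherapists (two) | Randomization and allocation | No: kept out of evaluations and reevaluations |
| Laboratory coordinator | Auditing | No: takes no part in data collection |
| Researcher who runs the randomization | Randomization and allocation | No data collection role described |
| Analyst | Statistical analysis plan | No: not involved in evaluations or treatment |
| Researcher responsible for the project | Ethics | Possible: keeps contact details, but has a different title |
| Evaluating physiotherapist | Data management; Statistical analysis plan | Yes: takes all measures and enters the data |

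The Statistical analysis plan section also calls the person who takes the measurements a researcher. The assessor is the best fit, by inference and not by statement.

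**2. Can a report reveal the arm?** Women know their treatment ("In view of the impossibility of blinding the participants in relation to the interventions"). NMES is given only in IG2, by a vaginal probe. A call about the current or the probe therefore identifies IG2. A non-specific complaint need not. The preceding sentence makes NMES-related pain a reason to discontinue, so whoever acts on the report has to establish whether the complaint comes from the NMES.

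**3. When?** Baseline measures precede randomization and are unaffected. The ten weekly sessions come next, then the post-treatment assessment. Data management assigns follow-up to the same physiotherapist, so knowledge gained during treatment would carry into the KHQ and SF-6D at months 3 and 6.

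**4. Which outcomes?**

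- Palpation is most exposed. Table 2 calls it subjective and gives an inter-rater kappa of 0.60.
- Manometry is labelled objective in Table 2, but the assessor instructs each maximal contraction.
- The KHQ, SF-6D and voiding diary are answered by women who know their arm. Assessor blinding protects these less, so its loss costs less.

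**5. How many women?** No adverse effect or unblinding rate is given. The ceiling is the size of IG2: 44 of 132, and 44 / 132 = 1/3. For orientation only, if 5% to 20% of IG2 women made a report that revealed the arm, the count would run from 44 × 0.05 = 2.2 to 44 × 0.20 = 8.8, about 2 to 9 women. Those rates are assumptions with no basis in the article.

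**The case against.** The strongest reply is that the central identity is inferred. The article uses several role titles, and Evaluation tools separates the responsible researcher from the physiotherapist who evaluates. The sponsor may have meant the former. This stands as a limit on certainty. It does not remove the need to correct the sentence, because staff who follow it as written could send reports to the assessor.

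A second reply is that NMES is given with a physiotherapist present and holding the probe, so pain during a session would usually reach the treating therapist first. That is fair and lowers the likely frequency. It does not cover effects noticed after the session, and the written instruction applies to any adverse effect.

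A third reply is that the primary outcomes are self-reported by unblinded women and the assessor-dependent measures are secondary. This stands and limits the consequence.

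A reader might also infer more than the article supports:

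- **That assessor blinding is the only blinding.** It is not. The treating physiotherapists are kept from the evaluation results, and the principal investigator's data set omits the allocation groups.
- **That harms are captured only by spontaneous report.** Harms auditing adds record review for all participants, although only for treatment-related harms.
- **That unequal contact makes the harms comparison uninterpretable.** During treatment IG1 and IG2 have 10 supervised sessions and the control group has none described, so uneven capture is a reasonable suspicion. But harms are not a listed primary or secondary outcome, no between-arm test of them is described, and how harms are elicited is detail that an article commonly leaves to the full protocol.

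**Conclusion.** The point holds as a conflict between the reporting line in Interventions and the Blinding section, on the natural but unstated reading that the recipient is the assessor. Following the instruction as written can unblind the assessor for an IG2 woman who reports an NMES-specific effect. It does not unblind the assessor across the trial.

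The effect is one-sided and bears mainly on palpation and manometry, then on the questionnaires that the assessor applies. Neither its frequency nor the resulting bias can be derived from the article. The conclusion rests on two assumptions: that the recipient is the assessor, and that some reports are specific enough to reveal the arm. The change is worth making because it removes an avoidable threat to a stated safeguard at almost no cost.

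**What to change.** 1. In Interventions, replace the recipient with a named role already in the plan that has no part in outcome assessment, and use the same contact in all three arms. One of the two treating physiotherapists would serve, provided that control women are given that contact too, since no treating physiotherapist is described for them. The laboratory coordinator is also outside data collection, but is the trial's auditor, and that independence is a reason to look elsewhere first.
2. Keep the adverse event log apart from the outcome file that the assessor enters.
3. Ask women at enrolment, and again before each assessment, not to tell the assessor which treatment they receive.
4. Reconcile Interventions, Blinding, Data management and Harms auditing so that they agree on who receives, records and reviews harms.
5. If a common harms question is added in all arms, someone other than the blinded assessor should ask it. If the assessor asked it on the monthly calls, the answers could unblind the month 3 and month 6 assessments.

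The cost is one changed contact line, a separate log and a short instruction to participants. The first four steps need no extra staff or visits, and they change neither the sample size nor the analysis.

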### Blinding

In view of the impossibility of blinding the participants in relation to the interventions, the blinding will happen among the physiotherapists, taking into account the evaluation and intervention. The physiotherapist who will carry out the evaluation will not have the information of the participants’ allocation, and the physiotherapists responsible for guide the interventions will not have the information referring to the evaluations and reevaluations of the participants.

### Minimizing missing data

To avoid and minimize missing data, all participants will receive reminders with the date and time for each session. Physiotherapists responsible for the interventions will also make calls to reinforce the scheduling of sessions. Regarding the evaluations and reevaluations, the blind assessor will contact the participant by telephone, at the end of the 10 treatment sessions, in order to define the best time and date for the reevaluation to be carried out.

### Data management

The data will be collected on paper and stored in folders in an office allocated at the Women’s Health Research Laboratory (LAMU), in Federal University of São Carlos. The data will be entered into the Excel software by the physiotherapist responsible for evaluations, reevaluations, and follow-up. In addition, all the data will be available in a public research bench.

The database and electronic analyzes will be stored on a secure computer server, with personal login access authorized by the principal investigator of the present study. The principal investigator will have access to the complete data set (without the allocation groups), and the co-investigators will have access to data when necessary. Upon completion of the study, all study data and documents will be archived by the main researcher of this study for 5 years at the Physiotherapy Department at Federal University of São Carlos.

### Data monitoring

We will conduct the study without a Data Monitoring Committee (CMD). PFMT, NMES, and home treatments are widely used in clinical practice and have proven to be acceptable. Since there is no CDM, we will not conduct an intermediate analysis during the clinical trial.

### Harms auditing

All participants’ medical records will be carefully evaluated, and all damages and complications related to treatments will be reported, if any. The damage will be classified as adverse events and their severity.

### Auditing

The coordinator of the laboratory where the research will be conducted will not participate in any of the research data collection steps. Therefore, she will be responsible for auditing and access to the final dataset all procedures that will be performed.

### Statistical analysis plan

The statistical analysis will be performed by a researcher without involvement in the evaluations and treatment intervention. The software SPSS 16.0 and R 3.5.1 will be used for the analysis of data. The level of significance will be set at 5%. The normality of the residues will be verified by the Shapiro-Wilk test.

The comparison of SUI, voiding habits, and quality of life between groups CG, IG 1, and IG 2 and between stages (pre-treatment, re-assessment after finished the intervention protocol and follow-up), as well as the interactions between groups, will be performed by means of analysis of variance (ANOVA) of mixed models considering group and time factors for repeated measures, if the residuals present normality with post hoc contrasts (group IG1 and IG2 versus group CG, and group IG1 versus group IG2).

The first statistical procedure will verify, in general and at each evaluation stage (pre-treatment, re-assessment after finished the intervention protocol and follow-up), if SUI urine loss per day related to stress (e.g., coughing, sneezing, physical exercise or household activities) and quality of life differ into the three groups. The null hypothesis is that all groups will present equal results during outcomes assessments. The alternative hypothesis is that IG 1 will differ from CG and that IG2 will differ from the CG as well.

The second statistical procedure aims to verify if there is alteration in the SUI, urine loss per day related to stress (e.g., coughing, sneezing, physical exercise or household activities), and quality of life throughout the four stages of study evaluation (pre-treatment, re-assessment after finished the intervention protocol and, follow-up of the 3rd and 6th month) within each of the groups. The null hypothesis is that the behavior is the same throughout the stages in each group. The alternative hypothesis is that there is a difference in the stages in each group.

The quantitative variables will be presented as minimum value, maximum value, mean, median, and standard deviation. Categorical variables will be presented as frequencies and percentages.

Details of the statistical analyzes are as follows:
At the interview and physical assessment, the subjective interview record will be applied, which generates qualitative variables that will be presented as frequencies and percentages and quantitative variables that will be presented as minimum value, maximum value, mean, median, and standard deviation. One researcher will perform the vaginal palpation and the manometry assessment, as well as applied SF6-D, KHQ, King´s Health Questionnaire for Scoring Algorithm, health cost analysis form, and 24 h-voiding diary, which will result in quantitative scales that will be presented as minimum value, maximum value, mean, median, and standard deviation.At the end of treatment sessions, vaginal palpation and manometry will be repeated, as well as SF6-D, KHQ, King’s Health Questionnaire for Scoring Algorithm, health cost analysis form, and the 24 h-voiding diary, which will result in quantitative scales that will be presented as minimum value, maximum value, mean, median, and standard deviation.At the 1st to the 6th month of follow-up, the health cost analysis form will be applied, and at the 3rd and 6th month of follow-up, the SF6-D, KHQ, King´s Health Questionnaire for Scoring Algorithm, and health cost analysis form will be completed, which will result in quantitative scales that will be presented as minimum value, maximum value, mean, median, and standard deviation.At the end of the treatment, the ANOVA for repeated measurements will be applied to verify the effects of the three groups and the two stages (pre-treatment and re-assessment after finished the intervention protocol) and the interactions between them according the results related to the vaginal palpation, manometry, SF6-D, KHQ, King´s Health Questionnaire for Scoring Algorithm, health cost analysis form, and 24 h-voiding diary, if the residues present normality. If the residues do not present normality, a non-parametric test will be applied.At the end of the follow-up, the repeated measures ANOVA will be applied to verify the effects of the three groups and the eight stages (pre-treatment, re-assessment after finished the intervention protocol and 1, 2, 3, 4, 5, and 6 months of the follow-up) and the interactions between them considering the SF6-D, KHQ, King’s Health Questionnaire for Scoring Algorithm, health cost analysis form, and 24 h-VD, if the residues present normality. If the residues do not present normality, a non-parametric test will be applied.The cost-utility assessment will be performed by the quality-adjusted life years (QALY), which combines the length and quality of life into a single index number between 0 and 1, where 0 corresponds to a health state judged to be equivalent to death and 1 corresponds to optimal health [35, 36]. To conduct the statistical analysis, the mean between-group cost differences will be corrected for their baseline, and the total costs will be divided by the costs differences for incremental analysis of cost-effectiveness and cost-utility ratios. Subsequently, a deterministic cost-utility value and a probabilistic one will be determined by applying a bootstrapping technique of 5000 interactions and the bias-corrected, in order to compare health costs between groups. The results will be presented with the confidence interval of 95% (95% CI). The likelihood of the cost-effective intervention will be estimated by the cost-effectiveness acceptability curves to compared values other than willingness to pay [37]. The Kaplan-Meier method and the Log-Rank between-group comparison test will be applied in order to assess the sensitivity of the uncertainty of each parameter by assessing the changes in the results in the range of parameter values [38].

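### KHQ and urine loss are compared by several tests, none named primary and none adjusted for baseline; the pooled test is diluted by the pre-treatment stage

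*Protocol article*

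**What the plan says.** All of this is in the protocol article, section Statistical analysis plan.

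- **Model.** "analysis of variance (ANOVA) of mixed models considering group and time factors for repeated measures", with post hoc contrasts of each intervention group against control and of the two intervention groups against each other. Pre-treatment is one level of the time factor.
- **First procedure.** "The first statistical procedure will verify, in general and at each evaluation stage (pre-treatment, re-assessment after finished the intervention protocol and follow-up"), whether urine loss and quality of life differ between groups. Its null: "The null hypothesis is that all groups will present equal results during outcomes assessments".
- **Second procedure.** Change over the stages within each arm. Its null: "The null hypothesis is that the behavior is the same throughout the stages in each group". Its alternative: "The alternative hypothesis is that there is a difference in the stages in each group".
- **End-of-treatment analysis.** A repeated-measures ANOVA "to verify the effects of the three groups and the two stages (pre-treatment and re-assessment after finished the intervention protocol) and the interactions between them". A similar ANOVA follows at the end of follow-up.
- **Baseline.** For the economic analysis, "the mean between-group cost differences will be corrected for their baseline". Nothing similar is stated for KHQ or urine loss.

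Randomization and allocation places the initial assessments before randomisation. Under Evaluation tools, the voiding diary is completed twice, before treatment and at the 10th session. KHQ is measured at four stages: baseline, end of treatment, and months 3 and 6.

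**The concern.** Before treatment, randomised groups have an expected difference of zero. A group effect averaged over stages that include pre-treatment is therefore smaller than the treatment effect. A group test at pre-treatment checks only the play of chance in the allocation.

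Tests of change within an arm mix treatment with natural course and regression to the mean, because women enter on the strength of current symptoms. All three arms are also told to exercise daily at home. A fall in every arm is likely and would say nothing about which arm is better.

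The tests that do address treatment, namely the stage-wise comparison at re-assessment and the interaction, leave the baseline value unused or use it inefficiently. Because no test is named as primary, procedures with very different power and meaning stand side by side, and the choice between them could be made after the results are known.

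**Working it through.** **Inputs.** From Sample size calculation: difference 5 KHQ points, SD 10, three groups, 5% level, power 85%, effect size f = 0.25, and 44 per group including 4 for loss, so 40 evaluated. Assumed: two-sided tests, the same SD at each stage, equal correlation ρ between stages, no multiplicity adjustment. The document does not give ρ. The range 0.36 to 0.82 is taken from the KHQ reproducibility coefficients in Table 2 as a proxy, with 0.5 as a central value.

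**1. The plan's own figure.** For a group main effect averaged over m stages, λ = f²·N·m / (1 + (m−1)ρ), with 2 and N−3 degrees of freedom. With m = 3 and ρ = 0.5, λ = 0.0625 × 120 × 3 / 2 = 11.25 and power is 0.851. N = 120 is the smallest equal-group size that reaches 85%, and adding 12 for loss gives the stated 132. A one-way ANOVA at a single stage with f = 0.25 has power 0.676 at N = 120 and needs 180. The stated size therefore matches a test pooled over three stages with the full effect at each. If the effect exists only after baseline, f becomes 0.25 × 2/3 and λ = 11.25 × 4/9 = 5.0, with power 0.49. Neither m nor ρ is stated, so this match is an inference.

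**2. Pooled test, one pair of arms.** The expected difference is 5(m−1)/m: 2.5 points with two stages, 3.75 with four. The variance factor of the average is (1 + (m−1)ρ)/m. At ρ = 0.5:
- m = 2: d = 0.25/√0.75 = 0.289; noncentrality 0.289 × √20 = 1.29; power 25%.
- m = 4, effect sustained: d = 0.375/√0.625 = 0.474; noncentrality 2.12; power 55%.

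**3. Undiluted tests, one pair of arms.** Variance factors relative to a single stage: post-only 1; change score (the pre/post interaction) 2(1−ρ); baseline-adjusted 1−ρ². With d = 0.5/√factor, noncentrality d√20 and 78 degrees of freedom:

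| ρ | Pooled, 2 stages | Pooled, 4 stages | Post-only | Change score | Baseline-adjusted |
|---|---|---|---|---|---|
| 0.36 | 27% | 63% | 60% | 50% | 66% |
| 0.5 | 25% | 55% | 60% | 60% | 72% |
| 0.6 | 24% | 51% | 60% | 70% | 79% |
| 0.75 | 22% | 45% | 60% | 88% | 92% |
| 0.82 | 21% | 43% | 60% | 96% | 97% |

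The adjusted variance divided by the change-score variance is (1−ρ²)/(2(1−ρ)) = (1+ρ)/2, which is below 1 for any ρ below 1. At ρ = 0.5 adjustment removes 25% of the variance of either alternative. By the normal approximation, 85% power then needs 54 per arm instead of 72.

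**4. Within-group tests.** Take two arms with the same true 5-point change, 40 each, ρ = 0.5. The SD of change is 10·√(2 × 0.5) = 10 and the SE is 10/√40 = 1.58, so power per arm is about Φ(3.16 − 1.96) = 0.885. The chance that one arm is significant and the other is not is 2 × 0.885 × 0.115 = 0.20, with no difference between the arms.

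**The case against.** A reader might infer that the plan has no post-treatment comparison between groups, or that the trial has only 25% power. The documents support neither. The sentence that sets out the first procedure also covers the re-assessment and follow-up, the group by stage interaction is planned, and pairwise contrasts are listed. Dilution touches neither the stage-wise tests after treatment nor the interaction. The main effect is routine output of a mixed ANOVA and is nowhere called decisive. The 25% applies to the two-stage analyses only: the diary, and the pre/post analysis of KHQ.

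Further points are fair. Change score and baseline adjustment are both unbiased under randomisation, and the gain shrinks to one percentage point at ρ = 0.82. Reproducibility coefficients are only a proxy for correlation across ten weeks of treatment. The first procedure's alternative is explicitly between groups, and nothing says that within-group significance will be taken as comparative effectiveness.

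A condensed article may also leave covariates to a fuller plan. But this section does more than stay silent: it fixes the model, the stages, the hypotheses and the contrasts, includes a pre-treatment group test, and mentions baseline correction for costs alone. What the objection leaves is a point about precision and clarity, not validity.

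**Conclusion.** The point holds as one of lost precision and a poorly ordered set of tests. The valid comparisons, post-only and interaction, give up power against a baseline-adjusted comparison at every correlation tried. The loss is 12 percentage points for both at ρ = 0.5. Against the change score it runs from 16 points at ρ = 0.36 to 1 point at ρ = 0.82; against post-only it grows with ρ, from 6 to 37 points. The pooled test is weaker still with two stages. With four KHQ stages and a sustained effect it is below the adjusted end-of-treatment contrast throughout, by 3 points at ρ = 0.36 and 17 at ρ = 0.5. The pre-treatment test is uninformative about treatment, and the within-group tests do not compare arms.

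The direction of the precision result does not depend on the value of ρ; its size does, and it also rests on a common SD of 10 and equal correlation between stages. That the trial was sized on the pooled test is plausible from the arithmetic but is not stated. The change should be made; the analysis as planned is not invalid without it.

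**What to change.** - **Primary analysis for KHQ:** a mixed model on the post-baseline stages with group, stage, group by stage and the baseline value of the outcome. The group contrasts at end of treatment are primary; those at months 3 and 6 are secondary. A model that constrains the baseline means to be equal across arms is an equivalent choice.
- **Urine loss from the diary:** ANCOVA on the single post-treatment measurement with its baseline value as covariate.
- **Drop** the group test at pre-treatment and the group test pooled over stages.
- **Within-group change:** report estimates with 95% CI, without p-values.

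The cost is a change to the analysis wording, made before the data are analysed. Baseline values of both outcomes are already collected, so no visit, measurement or participant is added.
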